### Evaluating the effectiveness of the AICP

2.8

The main effectiveness outcome will be the change from baseline to 12 and 24 months in the rates of mild-to-moderate AA episodes seen in PC and the PED in which patients are administered bronchodilators using a MDI with a spacer chamber. We will assess the overall effect of the AICP by testing the interaction between intervention and time of measurement. Should this intervention-by-time interaction be significant (with *p* < 0.05 as the threshold for significance), planned comparisons will be performed to determine whether changes in the AICP group between baseline and each of the follow-up points are significantly different from those observed in the control group. Secondary effectiveness outcomes will be the change from baseline to 12 and 24 months after the implementation of the AICP in: (a) rate of recording of Pulmonary Score at all levels of care; (b) rate of recording of asthma symptoms using the PACT at all levels of care; and lastly, (c) the change in rate of persistent asthma symptoms in children who initiate a background treatment at all levels of care.

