### Analysis

2.11

Frequencies and proportions along with the corresponding 95% confidence intervals (CIs) will be used to describe the rate of administration of bronchodilators using an MDI with a spacer chamber in paediatric asthma patients at all measurement points. The primary effectiveness outcome will be the changes in this bronchodilator use rate in children diagnosed with mild-to-moderate AAs in primary care, the PED, and hospital wards. To test the overall effect of the AICP, we will compare changes in outcome variables between the two groups over the three follow-up measurements adjusted for baseline values. Given the binary nature of most response variables (prescription rates or performing certain clinical practices/actions), the underlying regression model will be a logistic regression model, and hence, odds ratios or risk ratios will be calculated as estimators of the effect of the intervention. Multivariate mixed logistic models will be used to take into account the hierarchical structure of the data, with patients nested in paediatricians and/or health centres in each of the measurement periods (SAS PROC GLIMMIX ver. 9.4, SAS Institute, Cary, NC, USA, 2023). Separate models will be fitted for data from PC centres and EDs due to differences in the hierarchical structure of the data. In both PC and ED-related models, the AICP intervention, the time of measurement and intervention-by-time interaction will be included as fixed effects. Paediatricians and centres will be included as random effects in the intercept and the slope of the different repeated measurements in PC models, while a structure of patients nested in hospitals will be fitted for ED data, as patient care at EDs cannot be assigned to any specific physician. In all mixed models fitted, restricted maximum likelihood ratio tests and the Akaike and Bayesian information criteria will be used to estimate the modelled parameters (fixed and random), and to determine the best covariance structure for our data, respectively. Backward selection of effects with *p* < 0.05 as a threshold for inclusion and Laplace approximation will be used to identify parsimonious final multivariate mixed logistic models.

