**Figure 2 F2:**
[figure not shown]
SPIRIT schedule of procedures. AICP, asthma integrated care pathway.

Since data supporting the present study will mostly concern routine data retrieved from EHR of Osakidetza, it will be only shared on justified request to the study guarantors. The results of the study will be published in indexed scientific journals, regardless of whether they are positive, negative, or inconclusive at the end of the study.

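### The adjusted 12- and 24-month differences in change, which are the main outcome, are not secured if the intervention-by-time interaction is non-significant

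*Protocol article*

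**What the plan says.** Section 2.8 defines the primary endpoint: "The main effectiveness outcome will be the change from baseline to 12 and 24 months in the rates of mild-to-moderate AA episodes" in which a metered-dose inhaler with spacer is used. It then gives the test: "We will assess the overall effect of the AICP by testing the interaction between intervention and time of measurement". The between-group comparisons of change follow only under a condition. The sentence opens "Should this intervention-by-time interaction be significant", sets p<0.05, and continues that "planned comparisons will be performed to determine whether changes in the AICP group between baseline and each of the follow-up points" differ significantly from those in the control group. The section does not say what happens when the interaction is not significant.

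Section 2.11 (Analysis) adds four things, none of them tied to the interaction p-value:

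- "Frequencies and proportions along with the corresponding 95% confidence intervals (CIs) will be used to describe the rate of administration of bronchodilators" at all measurement points.
- For the overall effect, "we will compare changes in outcome variables between the two groups over the three follow-up measurements adjusted for baseline values". The interaction test therefore has several degrees of freedom.
- Odds or risk ratios will serve as effect estimators; no time point or contrast is named.
- Intervention, time and their interaction enter the models as fixed effects, but the final models come from backward selection at p<0.05, with no term exempted.

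**The concern.** A multi-degree-of-freedom interaction test gives neither the size nor the direction of the effect at 12 or 24 months. The quantity that does is the AICP change minus the control change at each time, with its CI. The plan places the comparison of that quantity behind the test and gives no fallback.

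Two things are at stake. First, section 3 says the results will inform scaling up to the whole regional service. If the interaction is not significant, that decision needs the interval for the effect, to see whether a useful improvement has been excluded or the data are merely inconclusive. Second, if time-specific effects were reported only when the gate opened, the reported values would be biased away from zero on average over repeated trials.

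**Working it through.** **1. What survives a non-significant interaction.**

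| Quantity | Promised unconditionally? | Gives the adjusted difference in change at 12 and 24 months? |
|---|---|---|
| Rates with 95% CIs per measurement point (2.11) | Yes | No. Separate proportions do not give the CI of a clustered, matched difference in change |
| Odds or risk ratios (2.11) | Yes | Not stated; no time point or contrast is named |
| Interaction coefficients of the full model (2.11) | Fitted at the start | Yes, on the log-odds scale with baseline as reference, but backward selection at p<0.05 may remove them |
| Planned comparisons (2.8) | No, only if interaction p<0.05 | Yes |

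**2. The plan's power figure.** Section 2.11 states 80% power for 15% against 10%, two-sided 5%, 1,100 primary care episodes per year in the intervention districts and clusters of 20 episodes. It gives no ICC, so 80% can be neither confirmed nor refuted. Solving for the design effect, DE = 1 + 19 × ICC, without continuity correction:

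- 1:1 needs 686 intervention episodes: DE = 1100/686 = 1.60, ICC = 0.60/19 ≈ 0.032.
- 2:1 needs 502 intervention episodes: DE = 1100/502 = 2.19, ICC = 1.19/19 ≈ 0.063.

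This power is for a two-sample comparison of proportions, not for the interaction test.

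**3. How often the gate opens.** Assumptions not in the document: DE 1.6 (1:1) or 2.2 (2:1), 10% in both groups at baseline, control rate flat at 10%, independent periods, the same true rate at every follow-up, and a normal approximation on the log-odds scale.

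For 1:1 the effective size is 1100/1.6 = 687.5 per group. Each group's log-odds has variance 1/[n p(1−p)].

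- Baseline contrast: v_b = 2/(687.5 × 0.09) = 0.0323.
- Follow-up contrast at 15%: v_f = 1/(687.5 × 0.1275) + 1/(687.5 × 0.09) = 0.0276.
- True log odds ratio: b = ln(0.15/0.85) − ln(0.10/0.90) = 0.463.
- Noncentrality with k follow-ups: λ = k b²/(v_f + k v_b). For k = 2 this is 0.428/0.0922 = 4.64; for k = 3, 0.642/0.1245 = 5.16.
- The chance that a noncentral chi-square with this λ exceeds its 5% critical value is 0.47 (2 df) and 0.45 (3 df).

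The 2:1 case (effective sizes 500 and 1,000) gives 0.47 and 0.45.

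**4. Average estimate given an open gate.** The ratio to the truth is P[χ²(k+2, λ) > c] / P[χ²(k, λ) > c], where c is the 5% critical value on k df. Simulation with 400,000 runs agrees.

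| True follow-up rate | Gate opens | Mean gated estimate / truth |
|---|---|---|
| 20% | 93–94% | 1.03 |
| 15% (planning value) | 45–47% | 1.35–1.38 |
| 13% | 20–21% | 1.8–1.9 |

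Ranges cover 1:1 and 2:1 matching and 2 or 3 df. Without the gate the mean estimate equals the truth (0.463 at the planning effect). In about 16% (2 df) to 26% (3 df) of runs at the planning effect, at least one time-point contrast is nominally significant while the gate stays closed.

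**The case against.** The strongest reply is that section 2.8 gates significance tests, not estimation. A global test before time-point tests is an accepted way to limit multiplicity. Section 2.11 promises rates with CIs and effect ratios without condition, and the fitted model already contains the differences in change. Moreover, when the interaction is significant, the 12- and 24-month estimates are the same numbers with or without the gate, and averaging only over significant trials inflates estimates under any design. Which model estimates get tabulated could be left to an analysis plan.

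Much of this stands, and it rules out three stronger readings that a reader might infer:

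- That the effects are calculated only when p<0.05. The text conditions the comparisons; it does not forbid estimation.
- That a significant trial necessarily reports an inflated effect. The inflation is an average over repetitions and is about 3% at a true rate of 20%.
- That the rule breaks the commitment in section 4 to publish results "regardless of whether they are positive, negative, or inconclusive at the end of the study". A non-significant interaction published with its rates is still a published negative result.

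What does not stand is that section 2.11 closes the gap. Its rates are descriptive, its ratios are tied to no time point, and its backward selection may drop the very coefficients the reply relies on. Nor is this merely detail deferred to another document: the conditional rule and the selection rule are both stated here, and both bear on the primary outcome.

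**Conclusion.** The point holds as a gap in what the plan guarantees. If the interaction is not significant, the adjusted difference in change with its CI at 12 and 24 months is not secured, although it measures the main outcome. That situation is quite plausible: at the planning effect, under the stated assumptions, the gate stays closed in about 53 to 55% of trials. The bias figures apply only if time-specific estimates were in fact withheld when the gate stays closed. They cover primary care only. They also depend on an assumed ICC, flat control rate and independent periods; positive correlation between periods within professionals would reduce the variance of a change and open the gate more often. The gap in reporting does not depend on any of these figures. It should be corrected, but it does not invalidate the design or the interaction test.

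**What to change.** - In section 2.8, state that the between-group difference in change from baseline, with its 95% CI, will be reported at 12 and 24 months (and at 36 months for maintenance) whatever the interaction p-value.
- Keep the interaction test as the gate for claims of statistical significance at individual time points only.
- In section 2.11, exempt intervention, time and their interaction from backward selection, so that the contrasts can always be estimated from the final model.

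The cost is about two sentences. The planned model already yields the contrasts, no further data are needed, and the multiplicity protection of the global test is kept.

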### Effectiveness objectives

1.1

To evaluate the effectiveness of the implementation of the AICP on: (a) increasing the rate of administration of bronchodilators using a metered-dose inhaler (MDI) with a spacer chamber in children diagnosed with a mild-to-moderate AAs in PC, PEDs, and hospital wards; (b) increasing the Pulmonary Score documentation rate at all levels of care; (c) increasing the rate of recording asthma symptoms using the Pediatric Asthma Control Tool (PACT) (31) in PC and PEDs; and (d) increasing the rate of initiation of background treatment in children with persistent asthma symptoms, in PC and PEDs.

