### Clinical intervention

2.5

The AICP is a structured multidisciplinary care plan that details the essential evidence-based steps in the care of patients with mild-to-moderate AAs and the coordinated practice of the agents involved as dictated by the evidence. In addition, the pathway determines the target population (inclusion/exclusion criteria); the sequence of common best practices during the patient's navigation through the system, according to the best available evidence in terms of: diagnostic methods and criteria, as well as their coding and recording; the provision of care and recommended clinical practices (actions, responsibilities, etc.); the educational activities for the patient and their relatives; the management of the patient and the patient's care; complex situations, management of difficulties and referral criteria; due attention to transitions between care levels and communication between professionals; and the outcomes to be pursued, evaluated and monitored.

In essence, the four core components of evidence-based clinical practice related to acute asthma as stated in the AICP (see Supplementary File S2) are:
•Assessment and recording of the Pulmonary Score;•Assessment and recording of asthma symptoms using the PACT;•Administration of background treatment in cases of persistent asthma symptoms;•Administration of bronchodilators using an MDI with a spacer chamber in children diagnosed with a mild-to-moderate asthma attack.The AICP was built on the model followed in the design of the Integrated Acute Bronchiolitis Care Pathway (29). It was developed based on the consensus of professionals involved in caring for children with asthma at different levels of care and the advice of experts in quality and medical documentation. Work started in 2020 and after an external evaluation process, its first version was approved in April 2021 (under editorial review).

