#### REACH

2.9.1

Absolute number and percentage of episodes of patients between 2 and 14 years presenting with an acute asthma episode during the study field period seen by any participating paediatric healthcare professionals exposed to the clinical practice established by the AICP for the management of AAs 12 and 24 months after its implementation, and their representativeness (characteristics of the participants compared to those of the target population). We consider that an episode has been exposed to the AICP if the patient has at least one of the recommended practices in an asthma episode registered: (a) assessment and recording of the Pulmonary Score; (b) assessment and recording of asthma symptoms using the PACT, (c) administration of background treatment in cases of persistent asthma symptoms, and/or (d) administration of bronchodilators using an MDI with a spacer chamber in children diagnosed with a mild-to-moderate asthma attack.

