#### ADOPTION

2.9.2

Absolute number and percentage of paediatric healthcare professionals adopting the AICP for the management of AAs 12 and 24 months after implementation, and their representativeness (characteristics of professionals/centres adopting the intervention/programme compared to those of professionals/centres potentially eligible to participate in the intervention/programme) (characteristics of adopters/non-adopters). We consider that a professional has adopted the pathway if he/she has registered at least one of the recommended practices in an asthma episode (assessment and recording of the Pulmonary Score; assessment and recording of asthma symptoms using the PACT; administration of background treatment in cases of persistent asthma symptoms; and/or administration of bronchodilators using an MDI with a spacer chamber in children diagnosed with a mild-to-moderate asthma attack) in at least 50% of the episodes attended. This adoption threshold, as a desirable goal for improvement, was proposed by the clinical committee within the research team and agreed with a representation of professionals from different levels of care after having considered baseline levels.

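### Secondary outcome (c) in section 2.8 does not measure objective 1.1(d): it conditions on starting background treatment instead of on having persistent symptoms

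*Protocol article*

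**What the plan says.** The letters differ between sections: objective (d) in section 1.1 corresponds to secondary outcome (c) in section 2.8, and objective (c), on PACT recording, corresponds to secondary outcome (b).

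- Section 1.1, objective (d): "increasing the rate of initiation of background treatment in children with persistent asthma symptoms, in PC and PEDs".
- Section 2.8, secondary outcome (c): "the change in rate of persistent asthma symptoms in children who initiate a background treatment at all levels of care".
- Section 2.5, core component of the pathway: "Administration of background treatment in cases of persistent asthma symptoms".
- Section 2.9.1, Reach, third qualifying practice: "c) administration of background treatment in cases of persistent asthma symptoms".
- Section 2.9.2, Adoption, among the qualifying practices: "administration of background treatment in cases of persistent asthma symptoms; and/or administration of bronchodilators using an MDI with a spacer chamber".
- Section 2.11, on the response variables in general: "Given the binary nature of most response variables (prescription rates or performing certain clinical practices/actions".

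Section 2.9.4 takes the primary and secondary effectiveness variables forward to assess change from 24 to 36 months, so the definition in section 2.8 is used again there.

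**The concern.** The objective asks whether more children who need background treatment are started on it. Its population is children with persistent symptoms, and its event is a treatment start. The outcome in section 2.8 takes treatment starters as its population and persistent symptoms as its event. The two proportions share a numerator count (children who have persistent symptoms and start treatment) but have different denominators, and they can move independently.

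If the outcome is analysed as worded, objective 1.1(d) has no effectiveness outcome that answers it, although it covers one of the four core components of the pathway. The wording also allows more than one definition, and the choice should not be left until the data are in view.

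**Working it through.** **Step 1: compare the definitions.**

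| Place | Population | Event |
|---|---|---|
| 1.1(d) objective | persistent symptoms | treatment started |
| 2.5 core component | persistent symptoms | treatment given |
| 2.9.1 Reach | persistent symptoms | treatment given |
| 2.9.2 Adoption | persistent symptoms | treatment given |
| 2.8(c) outcome, literal reading | treatment started | persistent symptoms |
| 2.8(c) outcome, other reading | treatment started | symptoms continue afterwards |

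Four places agree. Section 2.8 alone differs, on either reading. No section sets an objective about symptoms among treated children. Section 2.11 describes most response variables as prescriptions or clinical actions, which fits a treatment start and does not fit a symptom state.

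**Step 2: show that the two proportions are not interchangeable (literal reading).** The plan gives no figure for this outcome, so there is none to reproduce. All inputs below are assumptions, chosen only to show how the measures behave.

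Let 300 of 1,000 children have persistent symptoms. Let t be the proportion of these who start treatment, and u the proportion of the other 700 who start.

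- Objective: P(start | persistent) = t.
- Outcome as written: P(persistent | start) = 300t / (300t + 700u).

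Dividing through by 300t gives 1 / (1 + (700/300)(u/t)). For a fixed case mix, the written outcome therefore depends only on the ratio u/t and not on the level of t.

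*t rises from 0.30 to 0.60 with u fixed:*

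| u | Written outcome before | Written outcome after | Objective |
|---|---|---|---|
| 0 | 90/90 = 100% | 180/180 = 100% | 30% to 60% |
| 0.05 | 90/125 = 72% | 180/215 = 84% | 30% to 60% |
| 0.10 | 90/160 = 56% | 180/250 = 72% | 30% to 60% |

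The objective's rate gains 30 points in each row. The written outcome gains 0, about 12 and about 16 points.

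*Starting from 90 starts with persistent symptoms and 60 without:*

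| Scenario | Starts (persistent, other) | Objective | Written outcome |
|---|---|---|---|
| Baseline | 90, 60 | 90/300 = 0.30 | 90/150 = 0.60 |
| A: starts double in both groups | 180, 120 | 180/300 = 0.60 | 180/300 = 0.60 |
| B: only starts without persistent symptoms fall | 90, 10 | 90/300 = 0.30 | 90/100 = 0.90 |

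In A the objective is fully met and the written outcome shows nothing. In B the objective is not advanced and the written outcome rises by 30 points.

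**Step 3: the other reading.** If the sentence means symptoms that continue after treatment begins, it describes clinical response. The tables above do not apply to it, but it still says nothing about how many children with persistent symptoms are started on treatment.

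**Step 4: settings.** Objectives 1.1(c) and 1.1(d) name primary care and emergency departments. Secondary outcomes 2.8(b) and 2.8(c) name every level of care. The document does not say which scope is meant.

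**The case against.** The strongest defence is that this is a slip of the pen. The intended direction appears four times, and section 2.11 fits it. An analyst with the whole article would probably build the right indicator. That is fair, and it lowers the likely harm. It does not remove the contradiction: section 2.8 is where the outcome is defined, and no section restates the outcome correctly. Nor is this detail that an article leaves to a fuller document, because the article states the outcome and states it in a form that does not match its objective.

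The numerical illustration can also be challenged. Its counts are assumed, and the zero effect in the first table needs no child without persistent symptoms ever to be treated. In the other two rows of that table the written outcome moves in the right direction. This stands: the example proves that the measures differ and does not estimate harm in this trial.

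A reader might infer more than the text supports in four ways:

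- That the trial will certainly analyse the wrong quantity. The surrounding sections suggest otherwise, and the sentence has a second reading.
- That the main result is compromised. The primary outcome and the only power statement (10% against 15% for bronchodilator by inhaler with spacer) do not use this variable.
- That the registry entry carries the same error. It is not available here, so that cannot be said.
- That the narrower settings in section 1.1 are the correct ones. The authors could equally have meant to widen the objectives.

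**Conclusion.** The point holds as a mismatch between one secondary outcome and its objective. Under either reading, section 2.8(c) does not give the rate of treatment initiation among children with persistent symptoms. On the literal reading, the measured rate can stay flat while starts double, or rise by 30 points while starts in the target group do not change. Those sizes rest on assumed counts; the conclusion that the two measures can diverge follows from the formula and does not depend on them.

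The cause is most likely wording and not design. The reach is limited to this secondary outcome at 12 and 24 months and its reuse for the 24-to-36-month comparison. No stated figure in the article changes. The settings discrepancy for the PACT and background-treatment outcomes is real but separate and smaller, and the documents do not settle it.

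**What to change.** 1. In section 2.8, restate secondary outcome (c) as the change in the proportion of episodes in children with persistent asthma symptoms in which background treatment is initiated. The 24-to-36-month assessment in section 2.9.4 then takes up the corrected definition without further edits.
2. Decide which settings apply to the PACT and background-treatment outcomes, and use the same wording in sections 1.1 and 2.8.
3. Check whether the registry entry repeats the wording of section 2.8(c), and correct it only if it does.

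The cost is one sentence in section 2.8 and a short alignment of settings. The sample size, the primary analysis and the type of model are unaffected. The changes should be made and dated before this outcome is analysed. They concern the definition of an outcome only and imply nothing about how children should be treated.
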